## Abstract

**Background:**

Pain is a common debilitating symptom in cancer patients and its management remains a challenge. Among the non-pharmacological analgesic treatment options, low intensity transcranial electrical stimulation (tES) represents a new unique analgesic modality. However, the evidence of tES effectiveness for cancer pain is limited, while the mechanisms of pain relief due to tES are still poorly understood. We propose to test the efficacy of repetitive transcranial direct current stimulation (tDCS) and alternating current stimulation (tACS) in cancer pain patients, and attempt to understand their mechanisms using electroencephalography (EEG) and quantitative sensory testing (QST) measures.

**Methods:**

This article describes the protocol of a multicenter, sham-controlled, parallel-arm, triple-blinded randomized clinical trial assessing home-based tDCS and tACS in the treatment of cancer patients with persistent pain. 450 patients between 18 and 75 years old will be enrolled in this study. Treatment consists of 15 consecutive daily sessions of either anodal tDCS at 2 mA targeting the primary motor cortex or 10 Hz tACS targeting the dorsolateral prefrontal cortex. Following randomization (2:2:1 ratio), 180 patients will receive active tDCS, 180 patients active tACS, and 90 patients sham stimulation. The primary outcome is self-reported pain intensity on a numerical rating scale (NRS) assessed daily (15 days pre-treatment, 15 days during treatment and 15 days post-treatment). The secondary endpoints are medication intake, other cancer-associated symptoms and quality of life. We will also analyze psychophysical and neurophysiological correlates of ascending and descending pain processing using QST and EEG paradigms. Besides the NRS, which will be reported daily, assessments will be conducted at baseline (T0) and at three time points post-intervention (T1, T2, and T3).

**Discussion:**

Positive findings of the study will indicate the therapeutic benefit of tES in patients with cancer-related pain. Group differences in mechanistic measures would yield potential biomarkers for tDCS- and tACS-induced analgesia, which could be used for personalizing and optimizing the intervention. In addition, changes in EEG or QST could provide insights into the mechanisms underlying the tES effects.

**Trial registration:**

The study was registered at the German Clinical Trials Register under the identification number DRKS00031070.

## Introduction

Cancer-related pain—caused by tissue damage due to the cancer itself, metastases, or treatment—is one of the most common and most feared symptoms in patients with cancer [1–3]. Although the prevalence of pain in cancer patients has decreased in the last decade, it still ranges at high levels prevalence of cancer pain is still high, affecting 44.5% of the patients [4]. Cancer pain can persist for or emerge after months or years following treatment [5] and poses a significant burden on patients by impairing their quality of life, daily functioning, and social interactions [5]. Pain has been identified as one of the prognoses for shorter survival in patients, underscoring the necessity to better treat chronic cancer-related pain [6]. Despite the remarkable improvement in the detection and survival rate among different types of cancer patients in the last decades, cancer pain management remains a clinical challenge.

Until recently, the treatment of cancer pain involved primarily analgesic medication, with opioids being the mainstay [7], frequently leading to medication-abuse, dependence, and addiction [8, 9]. To achieve a more sustainable and personalized cancer pain management, the European Society for Medical Oncology recommends a multimodal treatment approach comprising primary antitumor therapy, analgesic treatment, and non-pharmacological and non-invasive therapeutic approaches [10].

Low intensity non-invasive transcranial electric stimulation (tES), especially repeatedly applied anodal transcranial direct current stimulation (tDCS) over the primary motor cortex (M1), has been successfully administered to treat chronic pain across a range of medical conditions, including fibromyalgia, chronic back pain, and neuropathic pain, among others [11–13]. tES, mainly comprising tDCS and transcranial alternating current stimulation (tACS), involves the application of a weak electrical current (1–2 mA) to the brain via surface electrodes placed on the scalp. Unlike tDCS, which involves a direct current with the ability to alter cortical excitability [14, 15], tACS entrains neuronal spiking activity by synchronizing the neural oscillations with the phase of the electrical stimulation through the application of a sinusoidal alternating current [16–18].

Compared to the array of guidelines and reviews on tES in other chronic pain conditions, those addressing the effectiveness of tDCS in patients with persistent cancer-related pain are limited [19–21]. Patients with hepatocellular carcinoma receiving 10 anodal M1-tDCS sessions reported reduced pain and depressive symptoms, with improvements lasting up to one month post-treatment compared to sham tDCS [22]. In patients with advanced head and neck cancer, 20 anodal M1-tDCS sessions significantly produced power spectra changes in several electroencephalography (EEG) bands immediately post-intervention, and pain relief associated with an attenuation of dysphagia and weight loss symptoms usually derived from chemoradiotherapy [23]. In an RCT, patients with primary malignant lung disease were treated with tDCS after going through a thoracotomy, apart from the patient-controlled intravenous morphine system [24]. The authors observed that patients treated with anodal tDCS consumed significantly less morphine during the post-thoracotomy period, compared to those who received sham stimulation. In a recent RCT, female patients with post-mastectomy pain syndrome received 5 sessions of anodal tDCS over M1 for 20 min on each side of the cerebral hemisphere, with those in the active group exhibiting reduced pain severity compared to the sham group [25]. The latest systematic review and meta-analysis on tDCS in pain management in cancer patients showed that anodal tDCS over the M1, left DLPFC, or insula area seems to be effective in reducing pain intensity in cancer patients undergoing surgery, compared to sham, but not in non-surgical patients [21]. Furthermore, tDCS seems to be more effective in pain relief in patients with greater pain intensity and in the long term. However, it is important to highlight that only six studies were included in the meta-analysis. Currently, a bi-center RCT is being conducted to test the effects of five sessions of anodal M1-tDCS on pain and quality of life in cancer patients receiving palliative care [26].

Until now, no study has explored the analgesic effects of repeated tACS in cancer patients with pain and only a few have tested the method in other pain conditions [27]. Ten sessions of 50 Hz tACS at 1 mA applied over the left M1 showed no pain reduction in fibromyalgia patients compared to sham [28]. We previously demonstrated that a single session of 140 Hz tACS delivered at 0.4 Hz over the visual cortex in migraine patients significantly lower pain severity in patients compared to sham tACS [29]. There is also preliminary evidence that a single session of 10 Hz tACS over the dorsolateral prefrontal cortex (DLPFC) delivered at 1 mA for 40 min can reduce pain [30, 31]. Nevertheless, the tES parameters are more heterogeneous for tACS across studies, in contrast to tDCS.

Home-based tDCS under remote supervision following adequate training in use of the technology, either self-administered or delivered by a caregiver, is feasible and safe in different patient populations, including knee osteoarthritis, fibromyalgia, migraine, and psychiatry disorders [32–38]. Thus, our study involves self-administered and remotely supervised at-home tES interventions, rather than clinic-based treatment to make the treatment more accessible to patients in terms of mobility. Quantitative sensory testing (QST) is a widely used psychophysical sensitivity test in clinical research, which assesses the patient’s perceptual response to calibrated stimuli and provides information about underlying mechanisms contributing to the pain sensation [39], having been validated across many chronic pain conditions [40]. Patients with cancer pain exhibit altered thermal detection and thermal pain thresholds compared to healthy controls [41]. Conditioned pain modulation (CPM) [42] and offset analgesia (OA) [43] paradigms, two measures of descending pain inhibition having distinctive mechanisms, have not yet been studied in cancer pain patients using QST. Complementarily, the temporal summation of pain (TSP) paradigm provides insights about pro-nociceptive mechanisms. These measures are included in our study protocol. In addition, we will also measure resting-state EEG and contact heat-evoked potentials (CHEPs), which is an established objective assessment of the function of Aδ and C fibers [44].

Our current multicenter RCT involving 450 cancer patients will be the largest in the literature to test the therapeutic efficacy of home-based tES, especially including both tDCS and tACS delivered for 15 consecutive days. The tDCS arm will receive anodal tDCS over M1. The tACS arm will receive active tACS at 10 Hz over the DLPFC and the control arm will receive sham stimulation (with either the tDCS or tACS montage). Patients and investigators will be blinded to stimulation type. Our primary aim is to test the impact of tES on pain relief and on the improvement of secondary symptoms and quality of life. Our secondary objective is to point out potential mechanisms underlying tES-mediated analgesia in cancer pain using concurrent EEG and QST. We also aim to identify and characterize responders to the intervention based on clinical variables and neurophysiological biomarkers.

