#### Visit 2. Baseline assessment (Study site; T0)

During the interview, sociodemographic (e.g., sex, age, lifestyle, medication pattern) and clinical data (comorbidities, type of cancer, extension, time since diagnosis, evolution, previous chronic diseases, risk factors for cancer, antecedents of cancer) will be collected.Patients will also fill in a battery of questionnaires on the web-based online PAINLESS platform (refer to Sect. 5.1 for further details) to assess pain and related symptoms (sleep quality, quality of life, fatigue…) and will take part in the QST and EEG measures. To avoid long assessment periods at the study site, participants will be offered the option to be interviewed online, via a secured videoconference platform and to fill in the questionnaires from home. Moreover, the relatives or caregivers will complete questionnaires addressing their quality of life, the burden of caring for the patients, and their socio-economic backgrounds. Following Visit 2, the patients will be randomly allocated to one of the three intervention groups, using the previously created randomization list. Both patients and clinicians/researchers responsible for the delivery of tES will be blinded to the treatment condition.

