### Specific aims and hypotheses

This multicenter study will address many aspects of cancer-related persistent pain including its potential treatment with repeated tES and assessment of the effectiveness of the therapy using self-reported assessment of different symptoms of the disease, psychophysical testing using QST and neurophysiological testing using EEG. The aims and hypotheses of the study are as follows:Aim 1: To determine the therapeutic effects of 15-day home-based anodal tDCS and tACS interventions (compared to sham stimulation) on pain intensity (primary outcome), other dimensions of pain (pain unpleasantness, catastrophizing, interference), quality of life, cancer-associated symptoms (fatigue, depression, anxiety, sleep fragmentation, cognitive impairment), and global functioning among patients with cancer-related persistent pain. We hypothesize that compared to sham, tDCS and tACS will reduce clinical pain and associated symptoms as well as improve quality of life and global functioning. We expect that anodal tDCS might have a stronger effect on pain intensity, while tACS can have a stronger effect of decreasing stress, emotional processing of pain and improving quality of life. We will also test the feasibility of the home-administered tES (analyzing dropout rates, satisfaction scores, adverse and side-effects…). The potential long-term benefits of the interventions will also be addressed at three and six months post-treatment follow-ups.Aim 2: To identify psychophysical and neurophysiological predictors and mediators of tES-induced analgesia in patients with cancer pain. We hypothesize that the improvement in clinical pain will be mediated by intervention-induced adaptive changes in (i) nociceptive and pain modulatory system using QST indices and through contact heat-evoked potentials (CHEPs) using concurrent heat painful stimuli and EEG, as well as (ii) in oscillatory activity measured by resting state EEG.Aim 3: To identify responders to the tES interventions based on clinically relevant reduction in pain intensity (≥ 30%) and to characterize them according to central pain biomarkers using QST, EEG measures and/or sociodemographic, climical and disease related data. We hypothesize that indices of pain modulation and perception will be sensitive to predict treatment outcomes.

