### Randomization and blinding

Following the informed consent and baseline evaluations, participants at each center will be locally randomized to the tDCS, tACS and placebo groups in a 2:2:1 allocation ratio, giving more weight to the active interventions. A staff member who is not involved in any study procedures will be responsible for creating the randomization list, generated by an automatic web-based randomization program from GraphPad Prism, and monitoring it during the study. The number of participants in the sham group was planned as half of those receiving tDCS or tACS. This 20% sham allocation was decided upon on account of it being the smallest and statistically correct number of patients that can stay without treatment. Given prior studies in populations with chronic pain, which showed clinically relevant remission of symptoms after tES treatments, we expect a positive effect of the technique in our trial [11]. The corresponding 20% of the sample is sufficient to achieve an analysis with sufficient statistical power. Therefore, for ethical reasons, we are keeping the size of the untreated group to a necessary minimum given our sample size.

The study will be triple-blinded, as the patient and caregiver, the study clinician and/or interventionist, and the evaluator will be blinded to the group assignment until the completion of the trial. The NeuroConn Data analysis will also be conducted in a blinded manner. The device used for the tES intervention (DC-STIMULATOR MOBILE, neuroConn GmbH, Ilmenau, Germany) allows complete blindness. Only the research members in charge of generating the randomization list will have access to the patient’s intervention status. The success of blinding will be measured at the end of the intervention by asking the patients what type of stimulation they think they received.

Unblinding will take place once recruitment and subsequent data analysis are completed. However, the coding system includes a mechanism that allows rapid identification of the treatment procedure in a medical emergency such as (1) in case of administration of an incorrect stimulation dose that could endanger the patient; (2) cases in which further treatment of the patient depends on knowledge of the treatment provided by the medical device;, and (3) in case of serious adverse events.

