*Anodal tDCS* The anode will be placed over the left M1 (C3, according to the 10–20 EEG system) and the cathode will be placed over the right orbito-ocular region (FP2). For the anodal tDCS, a constant current of 2 mA (20 min) with 15 s ramp-up and 15 s ramp-down at the beginning and the end of the stimulation period respectively was applied. The sham tDCS profile will constitute a 15 s direct current ramp-up to 2 mA, 15 s ramp-down to 0.05 Ma, 1130 s of 85 Hz sinusoidal current at 0.05 mA, at the beginning and end of the session, validated in [49]. *tACS* The electrodes will be placed in an F3-F4 montage over the frontal region targeting the DLPFC. A 10 Hz alternating current of 2 mA (peak-to-peak amplitude) will be applied for 20 min, with 15 s ramp-up and 15 s ramp-down. Participants in the sham group will have the same electrode montage as the tES protocols, with a ratio of tDCS to tACS montages 1:1. The sham sham tACS profile will constitute a 15 s 10 Hz sinusoidal alternating current ramp-up to 2 mA, 15 s ramp-down to 0.05 mA, and 1130 s of 85 Hz sinusoidal current at 0.05 mA, at the beginning and end of the session, validated in [50]. *Impedance quality* will be ≤ 15kΩ to ensure proper stimulation of the cortex. The application of tES follows consensus standards in the field, based on previously published guidelines [11, 51].

During each intervention session, participants will be instructed to assume a comfortable position (sitting or lying) and to rest (not to be involved in cognitive tasks or watching TV, but not sleep).

Each participant will receive 15 intervention sessions. The first tES session will take place in the study center (Visit 3), where the patient and/or caregiver will be trained by a researcher and/or clinical staff to operate and use the tES device and accessories. The patient will receive a tutorial handbook with a complete explanation of the procedures for stimulation and will also have access to an online video tutorial in their mother tongue. All supporting material will be available in the native language of the corresponding country. Then, the 14 stimulation sessions (two weeks) will be administered by the caregiver in the patient’s house or self-administered by the patient under remote supervision of the researchers.

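### tDCS and tACS use different electrode sites with no concealment described, so masking covers active v sham within a montage, not tDCS v tACS

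*Protocol article*

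**What the plan says.** Three places in the protocol article make the blinding claim:

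- Introduction: "Patients and investigators will be blinded to stimulation type".
- Visit 2: "Both patients and clinicians/researchers responsible for the delivery of tES will be blinded to the treatment condition".
- Randomization and blinding, which also names caregivers and patients: "the study clinician and/or interventionist, and the evaluator will be blinded to the group assignment until the completion of the trial".

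The section on transcranial electrical stimulation treatment fixes the electrode sites. For tDCS, the anode goes at C3 (left M1). The other tDCS electrode is at FP2: "the cathode will be placed over the right orbito-ocular region (FP2"). For tACS, "The electrodes will be placed in an F3-F4 montage over the frontal region targeting the DLPFC". Sham patients get one of these two layouts, "with a ratio of tDCS to tACS montages 1:1". The same section describes a cap with two electrodes. It mentions no dummy electrodes and no common layout that would hide which montage is in use.

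Session 1 is supervised at the clinic, where a researcher or clinical staff member trains the patient or caregiver on the equipment (Visit 3 and the stimulation section). The other 14 sessions are done at home.

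Under Specific aims and hypotheses, Aim 1 compares both active arms with sham. It then adds an expectation between the active arms: "We expect that anodal tDCS might have a stronger effect on pain intensity", with tACS expected to do more for stress, emotional processing of pain and quality of life. The Statistical analysis plan section uses a three-level group factor (tDCS, tACS, sham) with Bonferroni-Holm post hoc comparisons.

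**The concern.** A pre-programmed stimulator can hide whether current flows. It cannot hide where the electrodes are. If montage differs by modality, a patient with electrodes at C3/FP2 is on active tDCS or sham and never on active tACS. A patient with electrodes at F3-F4 is on active tACS or sham and never on active tDCS. Blinding to group assignment in a three-arm trial would require that all three options remain open, and they do not for anyone who can read the montage.

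At stake is how tDCS v tACS may be reported. The protocol expects a direction for that comparison on pain intensity, which is self-reported and so open to expectation, whether the patient's own or conveyed by staff who know the modality. Reporting that comparison as triple-blind would credit it with a protection the described design does not give.

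**Working it through.** **1. Inputs.** Allocation is 180 active tDCS, 180 active tACS and 90 sham, 450 in all (Abstract, Methods). Sham is split 1:1 by montage (stimulation section), so 90/2 = 45 sham patients wear each montage. The protocol gives no figure for the strength of blinding, so there is nothing of its own to reproduce.

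**2. Composition by montage.**

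| Montage | Active tDCS | Active tACS | Sham | Total |
|---|---|---|---|---|
| C3/FP2 | 180 | 0 | 45 | 225 |
| F3-F4 | 0 | 180 | 45 | 225 |

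The two zeros are the finding: each montage excludes one active arm.

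**3. What the montage reveals about active v sham.**

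- Before seeing the cap: P(active) = 360/450 = 0.80.
- After seeing the cap: P(active) = 180/225 = 0.80.

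These are equal, so the montage carries no information on this question.

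**4. What it reveals about the three-way assignment.**

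- Best guess without the montage (name either active arm): 180/450 = 40%.
- Best guess with the montage (name the matching active arm): (180 + 180)/450 = 360/450 = 80%.
- Among the 360 active patients, the modality is identified 100% of the time, against 180/360 = 50% by chance.

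The whole gain comes from separating tDCS from tACS.

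**5. Who is exposed.** Staff who supervise session 1 or train on the cap see the montage and know the protocol. Patients and caregivers handle the cap at home and are exposed if they recognise what the positions mean. The evaluator is named as a separate role under Randomization and blinding, and no section shows the evaluator seeing the cap. However, Visits 3, 4 and 6 use the same label, investigator, for supervising session 1, for the T1 interview and for the six-month call that collects the pain ratings. The article therefore does not show that the roles are kept apart.

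**6. Side question: pooled sham.** Let d be the difference in non-specific response between the two montages. The document gives no value, so d is an assumption. Pooled sham averages the two montages, so the tDCS v sham contrast shifts by +d/2 and tACS v sham by -d/2. Their average is unchanged, and tDCS v tACS carries the full d.

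- d = 0: shift 0.
- d = 0.5 NRS points: shift 0.25.
- d = 1.0 NRS points: shift 0.50.

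The standard errors, in SD units, for one active arm are:

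- v pooled sham: sqrt(1/180 + 1/90) = 0.129.
- v montage-matched sham: sqrt(1/180 + 1/45) = 0.167.
- Ratio: 0.167/0.129 = 1.29.

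**The case against.** The best defence is that stimulation type simply means real v sham. The Introduction says openly, just before the blinding statement, that sham uses either montage. The section on the online data management system gives the purpose of restricted access as keeping most clinicians from learning whether stimulation was real or sham. On that reading the design delivers what it promises and the defect is loose wording. This accounts for the Introduction, but not for the claim of blinding to group assignment in a trial with three groups.

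Several other points stand and limit the finding:

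- **Active v sham.** A reader might infer from the 0.80 figure that treatment status leaks. It does not: 0.80 follows from the 2:2:1 allocation and is the same with or without the montage.
- **Staff.** A reader might infer that all staff, evaluators included, are unblinded. The documents show only that staff supervise session 1 and train on the equipment. They do not say who fits the cap, or that the evaluator or the analyst sees it.
- **The device.** The statement that full blinding is possible is made about the stimulator, not about scalp positions, and need not be read as false.
- **The hypothesis.** The formal Aim 1 hypothesis is against sham. The statement about tDCS v tACS is a hedged expectation. It is still written down, and post hoc comparisons of a three-level factor would ordinarily include it.
- **Pooled sham.** A reader might infer that the active v sham contrasts are biased. Nothing in the documents suggests that sham response differs by montage.

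The planned question on which stimulation patients think they received helps to assess blinding afterwards. It does not create masking between the montages.

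**Conclusion.** The point holds in a limited form. As described, the trial masks active v sham within each montage. It does not mask tDCS v tACS for people who see the cap and can interpret it. For them one active arm is excluded with certainty, and the best three-way guess goes from 40% to 80%, while P(active) stays at 0.80. The blinding statements in the Introduction, under Visit 2 and under Randomization and blinding therefore claim more than the design gives.

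This rests on two assumptions: that the montages are distinguishable on the head, which the different sites imply, and that no concealment procedure exists beyond what the article describes. It does not support the conclusion that the trial is unblinded or that its comparisons with sham are compromised. The size of any resulting bias in tDCS v tACS cannot be worked out from the documents.

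**What to change.** 1. Reword the three blinding statements so that masking is claimed for active v sham within montage, and say that montage is visible to those who supervise, train on or apply the cap. If a procedure hides the montage, describe it instead.
2. Report any tDCS v tACS comparison, on pain or on the other Aim 1 outcomes, as not masked to montage for those who see the cap, and not as triple-blind.
3. State that the evaluator, already a separate role, does not handle the cap or receive montage information, and that this covers the T1 interview and the six-month call.
4. Optionally, report sham results by montage and add a montage-matched contrast beside the pooled one. Its standard error is about 29% larger, so it suits a sensitivity analysis rather than a replacement. It does not repair the tDCS v tACS comparison.

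The cost is protocol wording, some care over who does which visit, and at most one extra table. Sample size, visits and stimulation are untouched. The downside is a weaker blinding claim for one contrast.
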